#### 2.12. Planned start of the project

The theoretical and conceptual preparation of the study is already underway. The concrete preparation of the therapies and the sampling of the sample can be started at any time after a positive ethics decision has been issued; preferably from June 2021 onwards.

#### 2.13. Estimated total duration of the project

Total duration: 3 years: October 2020 - October 2023

- Preparation phase: October 2020 to May 2021
- Study period (implementation of the intervention, process evaluation, and follow-up measurement after three months): August 2021 to December 2022
- Evaluation of data December 2022 - February 2023
- Preparation of publications after completion of data collection as of February 2023
- Planned submission of the targeted cumulative dissertation: September 2023.

#### 2.14. Funding of the project?

none

### 3. project participants

#### 3a. Recruitment and exclusion

##### 3.1. Planned number of participants

According to Power calculation at least N=165 participants (see above)

3.2. Expected duration of participation in the planned project for individual participants (duration of the study dates; period)

24-26 weeks total: Intervention: 12 weeks, each with one 90- to 100-minute session and about 45 minutes of home exercises per week; follow-up another 12 weeks.

3.3. Characterization of participants

Minimum age: 18 Maximum age : 65

not personally capable of giving consent includable?

Yes No

Includable are

male and/or

female participants

3.4. Description of recruitment process (include all materials intended for use, e.g., advertisements):

Newspaper advertisements (have not yet been created), advertisements in online forums, internal university mailings, contacts to psychiatrists and psychotherapists, contacts to self-help groups, Facebook groups, Psychologie heute (Psychology Today).

3.5. Briefly describe the selection of participants and inclusion/exclusion criteria (sampling method, rationale, caseload estimate) (explicit rationale for inclusion of persons from protected groups, e.g., minors, temporarily or permanently incapacitated persons; if applicable).

Sample size as presented above, calculated using power analysis (G\*Power) criteria;  $p < .05$ ; 1-beta = .80; ES (between):  $d = 0.15 - 0.30$ ; 3 groups, 3 MZP. Required N=165 subjects, 55 per group.

Sample extraction: ad hoc/general sample; no other drawing is possible in this context.

Inclusion of protected groups not provided.

Inclusion criteria:

-age: 18 to 65

-Diagnosis of one of the following anxiety disorders: F40.1: Social anxiety disorder/social phobia; F41.0 Panic disorder with or without agoraphobia, F41.1 Generalized anxiety disorder.

-sufficient knowledge of German

-Average intellectual capacity (assessment during telephonic/video screening).

-Sufficient time for the weekly sessions and homework assignments.

-Acceptance of the study protocol

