"Therapy Tool for Anxiety Disorders" by Hagena and Gebauer (2014). The treatment manual of the control group is thematically based on that of Positive Psychotherapy, but strongly shortened. The treatment manuals of PPT and KVT each comprise 12 group sessions of 90-100 minutes each and one individual session. The treatment manual of the control group comprises 12 sessions, three of which (the first, the sixth and the twelfth) take place in an online group setting, and the remaining nine are self-completed with the help of instructional videos and e-mail communication. All therapy sessions take place online. The individual groups consist of six to eight participants. The participants in each group also have access to a website created specifically for the study. This website provides work materials, audio files and instructional videos. In addition, it offers the possibility of contacting the study director via a chat function; it also serves as a virtual bulletin board to make certain exercises visible in anonymized form. The study includes three measurement time points, a pre- and post-measurement and a follow-up after three months. The treatments are carried out by psychologists in training as clinical psychologists and psychological psychotherapists in Austria and Germany. All psychologists are intensively trained in the respective manuals, participate in regular intervision sessions and receive supervision from experienced representatives of Positive Psychology and Cognitive Behavioral Therapy at regular intervals. All group sessions are recorded and discussed in the supervision. Each session is checked for adherence to the manual. As mentioned above, the study also includes a process efficacy study. In this study the intra-session processes as well as the inter-session processes of the therapy with Positive Psychotherapy and Cognitive Behavioral Therapy will be evaluated and related to the therapy outcome. Intra-session processes are understood as all those changes that occur directly in response to specific events in the therapy session, whereas inter-session processes are defined as processes of change between two sessions that are brought about by memories and representations of the session (Orlinsky & Geller, 1993). Intra-session processes will be assessed with the help of the Berner Stundenbeurteilungsbogen für Patienten (Flückiger et al., 2010), where patients will be asked after each session whether they have experienced it and whether they think it has brought progress, on the one hand in the sense of the

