#### 2.4. Objective, questions, hypotheses (if applicable).

The effectiveness study aims to clarify the extent to which positive psychotherapy compared to cognitive behavioral therapy and a control group (online positive psychotherapy with minimal therapeutic support - hereafter referred to as "minimally supported online PPT") in patients with generalized anxiety disorder, social anxiety disorder/social phobia and/or panic disorder with or without agoraphobia (hereinafter referred to for brevity as "anxiety patients") can reduce anxiety symptoms and increase overall life satisfaction, quality of life, and happiness. Through this study, the effectiveness of Positive Psychotherapy in the treatment of anxiety disorders will be evaluated for the first time in an online format.

Research hypotheses:

- 1) The anxiety patients\* who participated in the Positive Psychotherapy treatment program showed a significant decrease in anxiety symptomatology between pre- and postmeasurement.
- 2) Anxiety patients who participated in the Positive Psychotherapy treatment program showed a significantly greater decrease in anxiety symptoms compared to patients who participated in the minimally supervised online PPT treatment program.
- 3) The anxiety patients\* who participated in the Cognitive Behavioral Therapy treatment program showed a significant decrease in anxiety symptomatology between pre- and postmeasurement.

- 4) Anxiety patients who participated in the Cognitive Behavioral Therapy treatment program showed a significantly greater reduction in anxiety symptoms compared to patients who participated in the minimally supervised online PPT treatment program.
- 5) The anxiety patients who participated in the Positive Psychotherapy treatment program showed a comparable decrease in anxiety symptoms as the patients who participated in the Cognitive Behavioral Therapy treatment program.
- 6) Anxiety patients who participated in the Positive Psychotherapy treatment program experience a significant increase in happiness between pre- and postmeasurement through direct influence on positive emotions, on recognizing and using one's strengths, and on experiencing meaning.

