## 2.6. Research Design

3x3 variance-analytic within-subjects design (within-subjects: repeated measures factor with three measurement time points: Pre, Post, Follow-up after three months). Between Subjects: Three treatment groups: two online.

conducted intervention and a low-level guided comparison group Controlled intervention study based on written treatment manuals; explicit inclusion and exclusion criteria (see below); rational sample design (see below); randomized patient assignment => RCT.

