## 2.9. Description of the sample (participants)

The sample size was calculated using a power analysis (G\*Power). This amounts to 165 subjects; accordingly, 55 subjects would be included in each of the three intervention groups. Regardless, the following inclusion and exclusion criteria are set for the study:

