#### 2.11. Description of the method of data analysis

SPSS: Changes from time point 1 to time point 2 and time point 3 are calculated using an ITT with hierarchical mixed linear models.

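### N=165 does not follow from 80% power at a between-group d of 0.15 to 0.30: as labelled, 55 per arm gives about 12% to 35% unadjusted power for the pairwise hypotheses

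*Protocol*

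**What the plan says.** Section 3.5 reports a G*Power calculation with p < .05, power .80 and an effect size labelled as between-group: "d = 0.15 - 0.30$ ; 3 groups, 3 MZP. Required N=165 subjects, 55 per group". Section 2.9 gives the same result, "This amounts to 165 subjects; accordingly, 55 subjects would be included in each of the three intervention groups", and section 3.1 repeats 165 as the minimum number of participants.

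Section 2.6 describes a "3x3 variance-analytic within-subjects design" with three treatment groups and measurements before treatment, after treatment and at three months. Section 2.11 says that changes are "calculated using an ITT with hierarchical mixed linear models".

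Six efficacy hypotheses in section 2.4 claim superiority of one arm over one other: 2, 4, 7, 8, 10 and 11. Hypothesis 2, for example, is that patients given positive psychotherapy "showed a significantly greater decrease in anxiety symptoms compared to patients who participated in the minimally supervised online PPT treatment program".

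The protocol does not state which G*Power test was run, which value in the range was entered, the correlation between repeated measurements, or whether the test is one- or two-sided.

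**The concern.** Required sample size varies with 1/d², so d = 0.15 needs (0.30/0.15)² = 4 times the patients that d = 0.30 needs. A single N cannot deliver 80% power at both ends. Moreover, 55 per arm is small for any standardised difference of 0.30 or less between two arms.

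The sample size is the ethics committee's evidence that the trial can answer its questions. If the true differences lie in the stated range and the power is well below 80%, most of the between-arm superiority hypotheses would be expected to end without significance, although the plan promises otherwise. An effect size with no stated test, metric or correlation also prevents anyone from checking the calculation.

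**Working it through.** **Inputs from the protocol.** Section 3.5: significance level 0.05, power 0.80, d = 0.15 to 0.30, 3 groups, 3 time points, N = 165, 55 per group. Section 2.4: the pairwise hypotheses.

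**Assumptions.** Two-sided testing. Baseline correlation r = 0.5 or 0.7 for adjusted comparisons, and repeated-measures correlation ρ = 0.5 for the F tests unless stated.

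**1. Can 165 be reproduced?** For a repeated-measures ANOVA with k = 3 groups and m = 3 times, the between-factors test has λ = f²·N·m / (1 + (m−1)ρ) on 2 and N−3 df.

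- f = 0.20, ρ = 0.5, N = 165: λ = 0.04 × 165 × 3 / 2 = 9.90, power 0.804.
- Same inputs, N = 162: λ = 9.72, power 0.796.

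So 165 is the smallest N with equal arms that reaches 80% at f = 0.20 and ρ = 0.5. Neither value is in the protocol. For three groups, f = 0.20 corresponds to a largest pairwise d of 0.20/0.471 = 0.42 to 0.20/0.408 = 0.49, depending on the pattern of means. Both exceed the stated d range.

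On the same test at N = 165:

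- Whole range read as f: λ = 0.0225 × 165 × 3 / 2 = 5.57 and power 54% at 0.15; power 99% at 0.30.
- Range kept as d and converted by f = d/2: 16.6% at d = 0.15 and 54% at d = 0.30.

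**2. Pairwise power with d as labelled.** Two-sample noncentral t with 108 df and noncentrality δ = d·√(n/2) / √(1−r²), where √(55/2) = 5.244 and r = 0 means unadjusted.

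| | d = 0.15 | d = 0.30 |
|---|---|---|
| Unadjusted | δ = 0.787, power 12.2% | δ = 1.573, power 34.5% |
| Adjusted, r = 0.5 | δ = 0.908, power 14.7% | δ = 1.817, power 43.7% |
| Adjusted, r = 0.7 | δ = 1.101, power 19.4% | δ = 2.203, power 58.8% |

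One-sided testing would not close the gap: unadjusted power is then about 19% and 47%.

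**3. Patients needed per arm for 80% power.** Unadjusted: 699 at d = 0.15 and 176 at d = 0.30, against 55 planned. Adjusted at r = 0.5: 525 and 132.

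**4. Detectable difference with 55 per arm at 80% power.** Unadjusted d = 0.54. Adjusted, it is 0.54 × √(1 − 0.25) = 0.47 at r = 0.5, and 0.54 × √(1 − 0.49) = 0.39 at r = 0.7.

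**5. The interaction test.** Here λ = f²·N·m / (1−ρ) on 4 and 2(N−3) df.

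- With f = d/2 and ρ = 0.5: λ = 0.075² × 165 × 3 / 0.5 = 5.57 and power 43% at d = 0.15; λ = 22.3 and power 98% at d = 0.30.
- That conversion does not represent a between-arm difference of d. Suppose both active arms differ from control by d at T2 and T3, and not at T1. Removing row and column means from the table of cell means leaves an interaction f of (2/9)d = 0.222d. At ρ = 0.5 this gives λ = 1.10 and power 11% at d = 0.15, and λ = 4.40 and power 35% at d = 0.30.

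**The case against.** The strongest reply is that the protocol declares a calculation for three groups and three time points, so checking it as a two-arm comparison at one time point tests something it never said it powered. On some G*Power set-ups the figure looks adequate:

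- The interaction test with f = d/2 and ρ = 0.5 gives 98% at d = 0.30 and 82% at the midpoint 0.225. At d = 0.15 it gives 43%, rising to 86% at ρ = 0.8.
- If the range is read as f on the interaction test, power is 98% even at 0.15 (ρ = 0.5).
- Averaging post and follow-up with baseline adjustment raises pairwise power to 60% at d = 0.30 with ρ = 0.5, 75% with ρ = 0.7 and 87% with ρ = 0.8. At d = 0.15 it gives only 20%, 26% and 34%.

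What stands is that 165 is not an arbitrary number, and that under some unstated choices part or all of the range reaches 80%. It would go too far to say that no calculation supports it. What does not stand is that these readings rescue the text. Each needs a test, metric or correlation that the protocol does not give, and the most favourable ones equate a between-arm d with an interaction effect that it does not produce. The hypotheses at issue are pairwise, so an omnibus calculation would not show their power in any case.

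It is also fair that hypotheses 1, 3, 6 and 9 concern change within one arm. The figures above say nothing about them.

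**Conclusion.** The concern holds for the effect size as labelled. With d = 0.15 to 0.30 and 55 per arm, the pairwise between-arm hypotheses have about 12% to 35% power unadjusted, 15% to 44% adjusted at r = 0.5, and 19% to 59% at r = 0.7. The unadjusted figures rest only on two-sided testing at 0.05 and full retention of 55 per arm. The adjusted ones also rest on an assumed correlation.

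Three stronger readings are tempting, and the document does not support them.

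- **That the sponsor certainly confused f with d.** The match at f = 0.20 and ρ = 0.5 is exact but inferred. The interaction route at d = 0.225 (f = d/2, ρ = 0.5) also comes close, with 80.7% power at N = 162.
- **That a specific further loss from dropout and clustering can be stated.** Section 2.3 says "The individual groups consist of six to eight participants", and section 3.5 mentions no dropout allowance. The protocol gives no intraclass correlation or dropout rate, so only the direction of the effect can be stated.
- **That a non-significant difference between positive psychotherapy and cognitive behavioural therapy would be taken as proof of hypothesis 5.** The protocol states no decision rule for that hypothesis, so this would be a prediction and a separate question from the arithmetic.

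**What to change.** Keep N=165. In sections 2.9, 3.1 and 3.5:

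1. Name the G*Power test, the metric (d or f), one effect size instead of a range, and the assumed correlation between measurements.
2. Delete the claim of 80% power at d = 0.15 to 0.30.
3. State that 55 per arm gives 80% power, at two-sided 0.05, for a pairwise difference of about d = 0.54 unadjusted, or 0.47 baseline-adjusted at an assumed correlation of 0.5 (0.39 at 0.7). Say that these figures are before any loss from dropout or therapy-group clustering.

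The cost is protocol wording, with no additional patients. The downside is that the stated detectable effect becomes less favourable. The sponsor would also need to say whether a difference of that size is plausible for the pairwise hypotheses.

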#### Exclusion Criteria:

-Participation in psychotherapeutic and/or psychological treatment or counseling, as well as participation in other psychological group services, planned at the same time or in the following three months.

-Symptoms of major depression, bipolar affective disorder or mania (current as well as history), psychotic, schizophrenic and/or schizo-affective disorders, chronic grief reaction, severe anorexia or bulimia, substance dependencies (alcohol, illicit drugs).

- severe personality disorders, especially borderline, narcissistic, anti/dissocial and paranoid personality disorder

- acute suicidality

- Switch, dose change, or complete discontinuation of psychopharmaka in the past or following three months.

Lack of decision making ability

3.6. Is consent obtained from participants (or their legal representative, if applicable)?

Yes (attach consent form)

No

If no, why not:

3.7. Proximity or dependency relationship between participants and investigators (e.g. student-lecturer, employee-employer, etc.). Is voluntariness guaranteed in this context?

There is no dependency relationship

3.8. How vulnerable are the participants from the submitter's perspective?

The test persons are people with increased psychological distress (social anxiety disorder, generalized anxiety disorder, panic disorder); accordingly, they are more vulnerable than psychologically normal people, but less vulnerable than people with severe psychotic, affective and/or personality disorders, who are excluded from the study. In this respect, their clinical vulnerability level is to be classified as medium.

### **3b. Data protection**

3.9. What personal data is collected?

Name, place of residence, e-mail address, telephone number, age, gender, marital status, education, nationality, psychometric data from clinical procedures, past psychotherapy(s), psychiatric treatment, intake of Psychotropic drugs

3.10. How should the anonymity of the participants be guaranteed?

Name, e-mail address and telephone number are required for organizational purposes and for sending the links for the online data collection. These data are recorded independently of the other - study-related - data only by the study director in an Excel spreadsheet and stored in a password-protected laptop. No other persons have access to it. All other data will be recorded pseudonymously via a trial personence code to be generated by the patients themselves (= individual code).

3.11. If complete anonymization is not possible, how is privacy protected?

Anonymity is to be protected on different levels. 1. At the level of the practitioner, it is protected by the professional laws. The therapists are subject to the confidentiality obligation according to the Austrian Psychologists' Act and the German Psychotherapists' Act. Accordingly, no information about the persons and their treatment may be disclosed to the outside. Only in the course of supervision and intervision may the contents of the units be discussed anonymously. However, the supervisors are also subject to the same professional laws as the therapists, so that the subjects' data is also protected at this level.

At the level of the research data, it is not possible to assign the data to a specific person due to the pseudonymization using individual codes; unless the person discloses their individual code.

On the level of the concrete personal data, anonymity is ensured by the fact that only the study director has access to these data and only he/she is aware of them; however, he/she is not able to assign the names to the data, as he/she does not have the individual codes. The personal data are accessible only to the study director through a password-protected table in an equally protected laptop.

3.12. How is it possible for participants to view their personal data?

Participants can only request access to their personal data from the study management by disclosing the individually issued code. Individual information and insight into the data and the individual results of the study can only be provided after the study has been completed in individual feedback sessions. For this purpose, however, the subjects must submit a request to the study director.

3.13. Can participants find out about the research findings?

☐ Ja      No If no, reason:

3.14. How and for how long can participants request the deletion of their data?

Upon request and notification of the individual participant's code, the data can be deleted. The deletion of the data can be requested until the end of the data collection. Afterwards, they are stored in a password-protected computer for further analyses and re-analyses.

3.15. The data processing takes place:

personal, justification:

Indirectly personal

How is anonymization performed?

Pseudonymization takes place via individually generated codes according to a six-digit key.

3.16. Are voices, sound, images or videos recorded?

☐ Ja      No

If yes: Consent of participants to be recorded? Yes

3.17. What are you doing to ensure that the participants from the study are able to opt out or withdraw their own data?

Already in the run-up and in connection with the recruitment, the participants are informed that they can withdraw or terminate their participation in the study at any time by means of a letter (e-mail) to the study management. This will exclude them from the study with immediate effect. At the beginning of the study, the participants will be given a

consent form is submitted or sent by e-mail (see appendix), in which this procedure and all other information about the study are described. If the withdrawal is associated with a request for deletion of the individual data, the individual code must be disclosed to the study management when communicating (e-mail).

3.18. How will the data be stored and/or destroyed after the project is completed?

The data are stored electronically and kept in an encrypted order of a password-protected laptop in pseudonymous form. The data are stored for 30 years. The data will be fully anonymized and used for further research. In the consent form, the participants are informed about the data processing and agree to it with their signature.

### **3c. Consequences for participants**

3.19. Risk and consequence assessment (e.g., pain, inconvenience, injury to personal integrity, and measures to avoid and/or provide for unforeseen/undesirable events).

In principle, undesirable side effects can occur during psychotherapy (Linden, & Strauß, 2018). The occurrence of undesirable side effects cannot be ruled out in the treatments planned here. However, the primary goal of the treatments is to reduce anxiety and general psychopathological symptoms and to improve general well-being and quality of life. According to the knowledge of previous studies, the risk of unpleasantness and negative developments in the field of PPT and KVT can be considered low. Cognitive behavioral therapy is the treatment of choice for anxiety disorders and has shown very good effects to date. Positive Psychotherapy aims to strengthen the resources and strengths of the participants. In the run-up to the treatment, the participants are informed that they should inform their therapists at any time if undesirable effects should occur. If the negative changes should not be reduced, the study management should be contacted by the patients or treatment providers.

In addition, participants are given the telephone number of the crisis service responsible for their area. If there are repeated complaints about adverse experiences or side effects of the therapies, a corresponding procedure for the systematic recording of such events will be implemented at the end of the treatment (T2) (e.g. INEP, Ladwig et al., 2014).

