5. The 12-week intervention based on the two manuals is conducted by psychologists in training as clinical psychologists or psychological psychotherapists in a dual trainer setting (two therapists). All therapists are intensively trained in

The group members are trained in the respective manuals, regularly update their work, and also receive regular supervision from experienced representatives of Positive Psychology and Cognitive Behavioral Theory. All group sessions are recorded and discussed in the supervision. Each session is evaluated for its adherence to the manual.

6. Before each therapy session, participants complete the Intersession Questionnaire (ISF) online for process analysis of the therapies, and after each session they complete the Patient Hourly Evaluation Form (STU-P) online.

7. The second questionnaire survey (T2) takes place after the last therapy session. For this purpose, the participants are sent the link to the online survey again. The same self-assessment procedures are used as for T1. This time, too, there will be an external assessment. This is done by the therapists using the Panic and Agoraphobia Scale (PAS) and the Hamilton Anxiety Scale (HAMA).

8. Three months after the end of the online groups, the participants receive another email with a link and a request to complete the questionnaire battery (=Follow-Up, T3). This time, too, the same self-assessment procedures are given as in T1 and T2. At this point of measurement, no further external assessment takes place.

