3.22. Methods to locate, record, and report adverse effects (Describe when, by whom, and how,  
z. e.g. free questioning and/or on the basis of lists)

During the weekly therapy sessions, undesired effects or side effects of the treatments can be immediately recognized by the therapists. The therapists are required to document not only the course of the session and the interventions, but also the perceived effects and feedback from the participants (especially negative and problem-related). In the case of communication of a negative development, this must be documented in particular; if the negative development is classified as problematic or dangerous, an individual discussion must be held promptly with the participant concerned. If no adequate solution can be found, the study and/or project management should be contacted in order to work out a solution (see also above). In addition, the intervention and the supervision of the therapists offer space to reflect on possible problems and problematic developments in individual participants and to obtain professional advice from trained clinical psychologists/psychotherapists. In addition, in the event of stress or undesirable developments outside or between treatment sessions, patients are able to contact the treatment providers at any time by e-mail or contact the study or project management.

3.23. If necessary: Plan for treatment and/or care after individuals have completed their participation in the project (who will be responsible and where).

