If problems or negative effects occur after the end of the treatments - in the follow-up period or afterwards - the participants are asked to contact the study or project management (but also the treatment providers can be contacted). If necessary, the participants can take advantage of a counseling session with these persons. The aim is to clarify the problems and work out individual solutions. It should also be determined whether the problems can be traced back to the treatment previously completed. In any case, the conversation should be documented. The solutions to the problems mentioned could include support for the person concerned in seeking help from a psychotherapist in the region, visiting their family doctor or a specialist themselves, or - in the worst case - making use of a crisis intervention center or medical facility, provided there is an indication for this. However, if necessary, the study or project management could also offer a further supportive intervention.

will be. Both are trained psychotherapists or psychotherapists in training.

3.24. Amount and procedure for the remuneration of participants (amount as well as how this is paid; e.g. travel expenses, loss of income, etc.).

No remuneration of the participants is foreseen; the participants receive free psychological treatment as indirect and immaterial remuneration (see above).

3.25. Amount and procedure for compensating participants (amount of payment and what it is paid for; e.g., pain, etc.)

The participants do not receive any compensation; no aversive stimuli are applied or severity caused.

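### Systematic side-effect recording starts only after an unquantified number of complaints and only at T2, so participant-attributed side effects cannot be compared fairly between arms

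*Protocol*

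**What the plan says.** **Systematic recording (3.19).** The rule is conditional: "If there are repeated complaints about adverse experiences or side effects of the therapies, a corresponding procedure for the systematic recording of such events" and this "will be implemented at the end of the treatment (T2"), with INEP given as an example. The protocol does not say how many complaints count as repeated.

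**During treatment (3.19 and 3.22).** Participants are told that "they should inform their therapists at any time if undesirable effects should occur". Independently of any complaint threshold, therapists must document the session and its interventions, "but also the perceived effects and feedback from the participants (especially negative and problem-related"). A negative development that is communicated must be specially documented. No standard question or checklist is named, although the form field asks when, by whom and how effects are found, with open questioning or lists as its examples.

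**After treatment (3.23).** "If problems or negative effects occur after the end of the treatments - in the follow-up period or afterwards", participants are asked to contact the study or project management. Whether the problem goes back to the treatment is to be clarified, and "In any case, the conversation should be documented".

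**Survey content (2.7 and 2.8).** At T3, "This time, too, the same self-assessment procedures are given as in T1 and T2", and "At this point of measurement, no further external assessment takes place". Neither the battery nor the outcome list contains a side-effect instrument.

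**Interruption (3.30).** Treatment is interrupted when at least 10% of participants show negative effects, and the study when more than 15% report a deterioration.

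**The concern.** An instrument that is switched on by complaints collects data selectively. Whether anyone is asked depends on earlier participants having spoken up, and on therapists or study management having judged those complaints to be repeated. Someone who finishes treatment before that point is not asked in a structured way. In follow-up nobody is, whether or not the trigger is met.

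The routes that remain depend on contact with a therapist or on the participant's own initiative, and contact differs by arm by design. A difference in recorded side effects between PPT, CBT and minimally supported PPT could then reflect the chance of detection as much as the treatments. The percentage rules in 3.30 need a count of affected participants, and no section says how that count is made.

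**Working it through.** The plan states no figure on this point, so there is none to reproduce. The check compares the sections, then uses some simple arithmetic.

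**1. Who is asked, when and how**

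| Period | Route | Unconditional? | Structured? |
|---|---|---|---|
| Treatment | Therapist documentation (3.22) | Yes | No |
| Treatment | Participant report to therapist, or e-mail (3.19, 3.22) | Open to all, participant-initiated | No |
| T2 | Side-effect procedure, e.g. INEP (3.19) | No, needs repeated complaints | Yes |
| Follow-up | Contact by participant, conversation documented (3.23) | Open to all, participant-initiated | No |
| T3 | Repeated self-report scales (2.7) | Yes | Yes, but symptoms and well-being only |

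No row is both unconditional and a structured question about side effects.

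**2. Live contact by arm (2.3)**
- PPT and CBT: 12 group sessions + 1 individual session = 13.
- Minimally supported PPT: 3 live sessions (1, 6 and 12); the other 12 − 3 = 9 are self-completed with videos and e-mail.

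Section 3.22 relies on therapists noticing effects in weekly sessions, which the third arm does not have live. Section 2.3 also leaves that arm out of the process study.

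**3. Participants past T2 before the trigger**

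Inputs: N = 165, 55 per arm; groups of 6 to 8; study period August 2021 to December 2022 (17 months); participation 24–26 weeks.
- Groups per arm: 55/8 = 6.9 and 55/6 = 9.2, so 7 to 9; over three arms, 21 to 27.
- Staggered starts fit the window, but the protocol describes no waves.
- None are missed if all groups reach T2 together with the trigger already met, or if the trigger comes before the first T2. All 165 are missed if it is never met.
- Illustration between these limits, assuming even starts over about 11 months: 12 weeks = 2.76 months, and the share past T2 at month m is (m − 2.76)/11. For m = 6: 3.24/11 = 0.295, or 49 of 165. For m = 9: 6.24/11 = 0.567, or 94 of 165. Both the start pattern and the trigger month are assumptions.

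**4. Counts behind 3.30**

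Taking all 165 as denominator (3.30 does not state one):
- at least 10%: 0.10 × 165 = 16.5, so 17 or more;
- more than 15%: 0.15 × 165 = 24.75, so 25 or more.

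Illustration for the first threshold: suppose 20% of participants truly have a negative effect and a fraction c of these is recorded. The number recorded is then Binomial(165, 0.20c), treating participants as independent.

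| c (assumed) | Expected count | Probability of 17 or more |
|---|---|---|
| 1.00 | 33.0 | about 1.00 |
| 0.75 | 24.8 | 0.97 |
| 0.50 | 16.5 | 0.49 |
| 0.25 | 8.3 | 0.004 |

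The documents give no value for c. The table shows only that the rule's behaviour depends heavily on how effects are recorded.

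**The case against.** The strongest reply is that 3.22, the section that governs adverse effects, already requires documentation from the first session without any complaint threshold. Sessions are recorded and discussed in supervision, and 3.23 requires follow-up contacts to be documented and their relation to treatment clarified. That stands. A reader might infer that harm data would exist only for late groups and only up to week 12, and the documents do not support this. Recording is unstructured during treatment and participant-initiated afterwards, but it is not absent.

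Other tempting readings go too far:
- **That the protocol expects late problems.** Section 3.23 is worded as a contingency, and 3.19 rates the risk as low.
- **That early cohorts are certain to be missed.** No cohorts are described.
- **That harm cannot be compared between arms at all.** The anxiety scales, PHQ-9 and ISR are given to all arms at T1, T2 and T3, so symptom worsening can be compared to three months.
- **That the trial leaves its benefit-risk statement in 3.29 untested.** That statement is a prospective opinion given to the ethics committee, not a hypothesis of the trial.

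It can also be said that a conditional instrument is a legitimate choice in a low-risk study, and that reporting by arm belongs in an analysis plan. The second part is fair. The first does not answer the unequal contact between arms: notes from 13 live sessions and from 3 are not comparable measurements, and no later analysis can repair that.

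**Conclusion.** The point holds in a limited form. The only structured side-effect measure depends on an undefined number of complaints and is placed at T2 alone. Side effects that participants attribute to treatment therefore cannot be compared fairly across the three arms, and in follow-up they are known only when a participant makes contact. This follows from the text without assumptions.

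The number of participants not systematically asked cannot be fixed from the protocol: it lies between 0 and 165, and the 29% and 57% above rest on assumed start dates and trigger months. The thresholds of 17 and 25 assume a denominator of 165, and the probabilities also assume a 20% true rate and a capture fraction. What is firm is that no unconditional, systematic count feeds 3.30, so 3.19, 3.22, 3.23 and 3.30 need to be reconciled on how negative effects are counted. Nothing here implies that the thresholds themselves are wrong. This is an inexpensive improvement to measurement and does not affect the efficacy comparison.

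**What to change.** 1. In 3.19, delete the condition on repeated complaints.
2. Include the kind of side-effect questionnaire already named there in the T2 and T3 online surveys of all three arms, from the first participant.
3. List it under secondary outcomes in 2.8, and add it to the T2 and T3 steps in 2.7.
4. Reconcile 3.19, 3.22, 3.23 and 3.30: state which records count as a negative effect or a deterioration, who keeps the count, and over which denominator. The questionnaire alone does not settle this, because it gives no count for participants still in treatment; the text must say how session documentation enters.

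The cost is a short amendment and one added questionnaire in two existing online surveys, a few minutes of participant time at each and no extra staff. More negative effects will be recorded than by complaints alone, which should be borne in mind when step 4 is written.
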